## Abstract

**Introduction:**

Osteoporosis (OP) is a growing global public health challenge, often underdiagnosed and underestimated due to limitations in current diagnostic tools such as DXA-based bone mineral density (BMD) assessment and FRAX score. These methods do not fully capture fracture risk nor account for gender-specific and metabolic differences. A novel patented diagnostic method, based on the *in vitro* behavior of peripheral mononuclear cells (PBMCs) may offer a more accessible, dynamic, and biologically representative approach to OP diagnosis and stratification.

**Methods and analysis:**

This multicenter, double-blind, cross-sectional clinical trial protocol aims to evaluate the diagnostic potential of the PBMC-based test using blood samples (2–5 mL) from 120 participants stratified by BMD (healthy, osteopenic, osteoporotic fractured and non-fractured). PBMCs are isolated and cultured *in vitro* to assess viability, number, size, and spontaneous osteoclast differentiation over time. Additionally, blood samples are analyzed for T lymphocyte subpopulations, pro- and anti-inflammatory cytokines, platelet-related parameters, and markers of bone turnover. All outcomes are analyzed considering gender differences. Correlation and accuracy analyses will determine the relationship between cellular and biochemical markers and OP status.

**Ethics and dissemination:**

The study protocol has been approved by Emilia Romagna’s Ethics Committee (CE-AVEC), Bologna, Italy. Written informed consent is obtained from all participants. Findings of this study will be disseminated through peer-reviewed publications and conference presentations.

**Clinical Trial Registration:**

https://clinicaltrials.gov/, identifier NCT06551155.

## Introduction

Osteoporosis (OP) is a major public health problem, and globally every 30 min one person suffers from an OP fracture, determining direct healthcare costs in Europe of about 37.5 billion (1). Although the World Health Organization (WHO) settles the OP diagnosis by Dual-energy X-ray Absorptiometry (DXA) T-score Bone Mineral Density (BMD) assessment, BMD alone has not enough sensitivity/specificity (2); many OP fractures occur with BMD values above OP diagnostic threshold, and test intervals, accuracy and targeted population are still debated (3). Additionally, Fracture Risk Assessment Tool FRAX, often associated with DXA and interesting for its modest cost, does not reach statistical strength needed to screen and identify OP fractures and stages. In addition to the above-mentioned limits linked to OP definition by DXA T-score, other restrictions exist. OP definition by DXA was developed for Caucasian women, although it has been used for other female populations and for men (4, 5). In addition to the well-known role of estrogen in women, which accelerates bone loss (5), men and women also display structural differences in bone growth, catabolism and size. The larger bone structure of men makes BMD results appear better than what they are (8). Likewise, aging men have more periosteal apposition, less cortical porosity and endocortical resorption than aging women (6). Thus, the same T-scores may mean different fracture risks in men and women of the same age. Additionally, T-scores results, both in men and in women, can be differently affected by the presence of co-morbidities (obesity, osteomalacia, etc). Therefore, BMD alone and/or associated with FRAX cannot represent an accurate predictor of OP and related fracture risk.

Inadequate screening, diagnosis and stage stratification may lead to an increased risk of OP fracture. In this context, advanced methods to support OP stages screening and diagnosis are mandatory (5). The main challenge is to develop tools at low cost and with low power consumption so that low-income countries may also benefit from them. A further requirement is that such technology may be hosted in a laboratory or a portable device; thus, isolated populations could also be assisted. Reliability of quantitative indices to support diagnosis is also important; thus, technology becomes independent of expert examiners’ availability. To try to react to this challenge, in 2018 a European patent has been deposited (IOR European patent n.3008470 March 21, 2018) referred to a method based on simple observation by light microscopy, in which the *in vitro* viability of circulating peripheral blood mononuclear cells (PBMCs) is related with altered bone metabolism and OP (7–9). Furthermore, specific gender related differences in number, dimension, differentiation time and gene and protein expression profiling of PBMCs from OP patients have been observed (9). In the light of these up-and-coming results, this PBMCs-based diagnostic test might complement the existing protocols, giving the possibility to screen and stratify different stages of OP through a common blood collection, feasible simultaneously with routine serum evaluations, also proposing a solution that might reduce gender disparities in OP disease. In this context, the significance of this protocol is to expand and fully develop this patent by a) improving the knowledge and mechanism of actions of the observed PBMCs behavior on which the patented OP tool is based; b) relating the PBMCs *in vitro* behavior with different levels and severity of altered bone metabolism (from osteopenia to bone fragility fractures); c) evaluating the combination of other blood factors measurement linked to OP status (i.e. platelet related parameters, pro- and anti-inflammatory cytokines, lymphocyte subpopulations) to strengthen the reliability of the method. We hypothesize that by answering and highlighting all these unaddressed inquiries this method could represent an advanced and simple strategy to screen, monitor and above all stratify the population at risk of OP and fractures. This test could be done simultaneously and in combination with regular blood tests, without any additional time and with only 2–5 ml of supplementary blood. This advanced method will deliver a safe, effective, sustainable, high-quality, low power consumption, and patient-friendly tool with a maximum health care impact, providing a ‘One-Health’ strategy for OP disease. This claim is supported by the minimally invasive nature of the test (small peripheral blood draw, no radiation), its compatibility with routine laboratory workflows, and its potential scalability to portable, low-power devices.

### Objectives and trial design

#### Primary objective

To analyze the viability, number, size, and differentiation time of PBMCs isolated from peripheral blood samples (2–5 ml) of non-osteopenic and non-osteoporotic patients (hereafter referred to as healthy patients), osteopenic patients, and osteoporotic patients (both fractured and non-fractured) with available DXA or, for fractured patients, DXA prescribed as per clinical practice for secondary prevention.

The aim is to evaluate the sensitivity and specificity of a diagnostic test based on the *in vitro* maintenance and differentiation of PBMCs (European Patent IOR No. 3008470, March 21, 2018) through a multicenter cross-sectional clinical study. Patients are stratified based on their BMD DXA T-score into osteoporotic, fractured and non-fractured (BMD T-score: < -2.5), osteopenic (BMD T-score: -2.5 < T-score < -1), and healthy (BMD T-score: ≥ 1). In accordance with secondary prevention guidelines, patients with a fragility fracture are categorized as ‘osteoporotic fractured’, irrespective of their exact BMD T-score. All assessments are conducted also considering specific gender differences.

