### Allocation

Participants are stratified based on their bone mineral density (BMD), assessed by dual-energy X-ray absorptiometry (DXA) at the hip and lumbar spine. Stratification follows WHO criteria, resulting in three main groups:

- Osteoporotic patients (T-score < -2.5 SD), further divided into fractured and non-fractured subgroups;- Osteopenic patients (-2.5 SD < T-score < -1 SD);- Healthy controls (T-score ≥ -1 SD).

A total of 120 participants are enrolled, with 30 individuals allocated to each of the four resulting subgroups (osteoporotic fractured, osteoporotic unfractured, osteopenic, and healthy). Allocation is performed upon confirmation of DXA availability and based on T-score values. No randomization is applied, as group assignment depends on predefined diagnostic criteria.

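### The Primary objective and Allocation sections give conflicting T-score rules: healthy is ≥ 1 in one and ≥ -1 in the other, exactly -2.5 has no group in either, and fractured patients are classified differently

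*Protocol article*

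**What the plan says.** All of this is in the Protocol article.

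**Primary objective.** Healthy participants are first described in words: "non-osteopenic and non-osteoporotic patients (hereafter referred to as healthy patients". The numerical cut-offs follow. The lowest group is "osteoporotic, fractured and non-fractured (BMD T-score: < -2.5" and the other two are "osteopenic (BMD T-score: -2.5 < T-score < -1), and healthy (BMD T-score: ≥ 1". The next sentence adds a fracture rule: "patients with a fragility fracture are categorized as ‘osteoporotic fractured’, irrespective of their exact BMD T-score". The section also states what the groups are for: "The aim is to evaluate the sensitivity and specificity of a diagnostic test".

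**Allocation.** This section says that it follows WHO criteria, and it lists three groups: "Osteoporotic patients (T-score < -2.5 SD), further divided into fractured and non-fractured subgroups"; "Osteopenic patients (-2.5 SD < T-score < -1 SD"; and "Healthy controls (T-score ≥ -1 SD". It then sets 30 participants in each of four subgroups, assigned by T-score, and does not mention the fracture rule.

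**Elsewhere.** The inclusion criteria name the groups but give no cut-offs. The Statistical methods section stratifies by T-score and gender and plans correlation, regression and accuracy analyses on that basis.

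**The concern.** The test is to be judged by sensitivity and specificity, so each participant needs one unambiguous disease status. The T-score groups are the only such status that the article gives. Two current sections define them, and they disagree on who is healthy and on how a fracture counts. Neither covers every T-score.

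The healthy cut-off matters because specificity is estimated in that group. If ≥ 1 were applied, the controls would start 2 T-score units above the upper limit of osteopenia (from -1 to 1). If PBMC behaviour tracks bone density, such extreme controls are easier to separate from cases, and specificity and the area under the ROC curve (AUC) would tend to be too high.

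The fracture rule matters because it decides who belongs in one of the four planned groups of 30. It also decides whether some fractured patients would otherwise be counted as osteopenic or even healthy.

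Two sites recruit. Enrolment began on 30 August 2024, so participants may already have been classified.

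**Working it through.** **Step 1. Apply each rule as printed.**

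| T-score | Non-fractured, Primary objective | Non-fractured, Allocation | Fractured, Primary objective | Fractured, Allocation |
|---|---|---|---|---|
| -2.6 | osteoporotic | osteoporotic | osteoporotic fractured | osteoporotic fractured |
| -2.5 | **none** | **none** | osteoporotic fractured | **none** |
| -2.4 | osteopenic | osteopenic | osteoporotic fractured | **osteopenic** |
| -1.1 | osteopenic | osteopenic | osteoporotic fractured | **osteopenic** |
| -1.0 | **none** | healthy | osteoporotic fractured | **healthy** |
| -0.9 | **none** | healthy | osteoporotic fractured | **healthy** |
| 0 | **none** | healthy | osteoporotic fractured | **healthy** |
| 0.9 | **none** | healthy | osteoporotic fractured | **healthy** |
| 1.0 | healthy | healthy | osteoporotic fractured | **healthy** |

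The table shows three things:

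- **Healthy cut-off.** For non-fractured people the sections differ only for -1 ≤ T < 1. That range has no group under the Primary objective and is healthy under Allocation.
- **Exactly -2.5.** A non-fractured participant has no group under either section. Correcting the sign of the healthy cut-off does not change this.
- **Fracture.** The sections agree only for T < -2.5. At every T-score from -2.5 upwards they give different answers.

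**Step 2. Compare the Primary objective with itself.** In words, healthy means neither osteopenic nor osteoporotic. Its osteopenic range ends at -1. A non-fractured person at T = 0 is therefore healthy by the words and ungrouped by the number. The words fit ≥ -1, except that they would also take in exactly -2.5. They do not fit ≥ 1.

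**Step 3. Illustrate the size.** The article gives no T-score distribution. I assume a normal distribution with mean m from 0 to -1.5 and SD s from 1.0 to 1.2, and reporting to one decimal.

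- Share of those healthy under ≥ -1 who are ungrouped under ≥ 1: 1 − P(T ≥ 1) / P(T ≥ -1).
- Share of all people whose T-score rounds to -2.5: Φ((-2.45 − m)/s) − Φ((-2.55 − m)/s).

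| m | s | Ungrouped share of those with T ≥ -1 | Rounds to -2.5 |
|---|---|---|---|
| 0 | 1.0 | 0.811 | 0.0018 |
| 0 | 1.2 | 0.746 | 0.0038 |
| -0.5 | 1.0 | 0.903 | 0.0054 |
| -0.5 | 1.2 | 0.840 | 0.0083 |
| -1 | 1.0 | 0.954 | 0.0130 |
| -1 | 1.2 | 0.904 | 0.0152 |
| -1.5 | 1.0 | 0.980 | 0.0242 |
| -1.5 | 1.2 | 0.945 | 0.0235 |

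For example, at m = 0 and s = 1.0, P(T ≥ 1) = 0.159 and P(T ≥ -1) = 0.841, and 1 − 0.159/0.841 = 0.811. Over the grid, the first share runs from about 75% to 98% and the second from about 0.2% to 2.4%. Per 120 people assessed, the second is 120 × 0.0018 ≈ 0.2 to 120 × 0.0242 ≈ 2.9 people.

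**Step 4. Check the sample size.** The stated inputs are w = 0.33, alpha 0.05, power 0.80 and 20% drop-out. Four groups by yes/no viability give 3 degrees of freedom. With noncentrality N × w², power reaches 0.80 at N = 101, and 101 × 1.2 = 121.2, close to the planned 120. No T-score cut-off enters this calculation.

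**The case against.** The strongest reply is that the document largely settles the healthy cut-off itself. Allocation is the section that governs assignment to groups. It prints ≥ -1 and names the WHO criteria, and the verbal definition in the Primary objective agrees. On this view there is one slip in an objectives paragraph and the working rule is intact. The article also condenses a fuller protocol that sites would use. This mostly stands: a dropped minus sign is the likeliest explanation.

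A reader might go further and infer that the trial recruited unusually dense-boned controls, or that its specificity and AUC are inflated. The documents do not support that. The bias arises only if a site applied ≥ 1 against both Allocation and the section's own words, and nothing indicates that any site did. Nor do they support saying that everyone with -1 ≤ T < 1 is ungrouped under the Primary objective, because its fracture rule catches fractured patients at any T-score.

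It can also be said that -2.5 is a single value and affects few people. That is fair as to size. But T-scores reported to one decimal can take that value, and the typing-error explanation does not cover it, since Allocation has the same gap.

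Finally, Allocation could be read as shorthand, with the fracture rule applied first. That reading is possible, but the section does not say so. It places fractured patients inside T < -2.5 and bases assignment on T-score.

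**Conclusion.** The point holds as an inconsistency in the written classification. It does not show that the wrong participants were enrolled.

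- **Certain from the text:** the two healthy cut-offs differ by 2 T-score units; a non-fractured T-score of exactly -2.5 has no group in either section; and the sections classify fractured patients differently at every T-score from -2.5 upwards.
- **Probable:** the printed ≥ 1 is a lost minus sign.
- **Conditional:** inflated specificity and AUC, only if ≥ 1 was actually applied.
- **Illustrative only:** the 75% to 98% and the 0.2% to 2.4%, which rest on an assumed normal distribution and, for the second, on one-decimal reporting.

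The fracture conflict should not be overlooked beside the more visible sign error. It bears on the make-up of a whole group of 30, and correcting the cut-offs alone would still leave two rules. The article does not say how many fractured participants have T ≥ -2.5, so the number affected cannot be given.

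**What to change.** 1. In the Primary objective, change the healthy cut-off to ≥ -1, to match Allocation and the section's own verbal definition.
2. In both sections, make exactly one of the two bounds at -2.5 inclusive. Allocation says that it follows WHO criteria, so the bound should be taken from that definition and written out, since the article does not reproduce it.
3. Reconcile the fracture rule between the two sections, so that one exhaustive, non-overlapping classification applies. Which rule to adopt is for the investigators to decide.
4. Check enrolled participants against the single rule. The records to look at are fractured patients with T ≥ -2.5, non-fractured participants at exactly -2.5, and non-fractured participants with -1 ≤ T < 1.

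The cost is a few words in two sections and a review of existing case report forms. The sample size calculation stays as it is. Depending on how the fracture rule is reconciled, some participants may move between groups.

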#### Secondary objectives

Ø To characterize lymphocyte subpopulations, platelet-related parameters, inflammatory status, and routine biochemical markers of bone turnover in blood samples from patients involved in the multicenter cross-sectional clinical trial. All experiments are conducted considering specific gender differences.Ø To investigate the relationship between BMD and PBMC properties *in vitro* in terms of viability, number, size, differentiation time, lymphocyte subpopulations, pro-inflammatory cytokines, and biochemical markers of bone turnover, also stratifying by gender, through a correlation study.

This integrative approach aims to overcome the limitations of single-parameter diagnostics, and its reliability will be evaluated through correlation and accuracy analyses, including ROC curves.

## Methods and analysis

### Study setting

The study is a multicenter cross-sectional clinical trial, with activities related to the study performed at two sites (IRCCS Istituto Ortopedico Rizzoli, Bologna, Italy and Azienda Ospedaliero Universitaria Policlinico G. Rodolico-San Marco, Catania, Italy). This trial protocol was produced according to the Standard Protocol Items: Recommendations for Interventional Trials (SPIRIT) reporting guidelines (10).

### Patient and public involvement

Patients contributed to raising research questions by prompting clinicians to find solutions to their BMD and fracture risk. Patients were not involved in planning the design of the study and outcome measures, which were decided according to the field scientific standards.

### Eligibility criteria

Patients are recruited according to the following criteria.

#### Inclusion criteria

Ø Healthy, osteopenic and OP (fractured and unfractured) patients;Ø Available DXA (hip and/or lumbar spine) BMD T-score;Ø Men or women > 40 years from two different Italian areas (Bologna, Catania);Ø Body Mass Index (BMI) between 18.5-29.9 Kg/m^2^;Ø Informed consent signed.

#### Exclusion criteria

Ø Hematopoietic system diseases;Ø Bleeding disorders;Ø Infections (also positive for HIV-HBV-HCV);Ø Neoplastic pathologies;Ø State of pregnancy or breast-feeding;Ø Alcohol use (>20g alcohol per day currently or previously);Ø Smoking (>10 cigarettes per day currently or previously);Ø Diabetes.

Smoking and diabetes conditions were excluded to minimize major confounding effects on immune, metabolic, and inflammatory parameters that could interfere with the interpretation of PBMC behavior independently from bone status.

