## Strengths and limitations of this study

*-Innovative Diagnostic Approach*.

This study investigates a novel, patented PBMC-based method for OP screening and stratification. By relying on simple blood collection and *in vitro* PBMC behavior, this approach offers a potentially accessible, low-cost, and portable alternative to current diagnostic tools such as DXA and FRAX, which show important limitations.

*-Gender-Specific and Multi-Parameter Evaluation*.

A key strength is the integration of gender-specific analysis and the correlation of PBMC behavior with platelet indices, lymphocyte subpopulations, inflammatory cytokines, and bone turnover markers. This comprehensive profiling may lead to a more precise understanding of OP pathophysiology and risk across different patient subgroups.

*-Double-Blind Design and Multicenter Validation*.

The study design includes a partial double-blind approach to reduce laboratory and interpretation bias, and involves two geographically distinct centers in Italy, strengthening the reproducibility and generalizability of results across different populations.

*-Non-Randomized Design*.

A limitation is the non-randomized nature of the study, which does not allow for assessment of causality or longitudinal changes. While stratification is rigorous, observational bias cannot be entirely ruled out.

*-Restricted Population and Potential Confounders*.

Although several confounding factors (e.g., BMI, comorbidities, substance use) are excluded by design, the inclusion of only patients with recent DXA and a limited age range (>40 years) may reduce generalizability to younger populations or those without DXA access.

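### Osteomalacia is named as affecting T-scores but is not excluded from a T-score-based reference class, and active inflammatory disease is left uncontrolled

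*Protocol article*

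**What the plan says.** The Introduction, in its account of the limits of DXA, says that T-scores in both sexes "can be differently affected by the presence of co-morbidities (obesity, osteomalacia, etc").

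Under Primary objective, the reference classes follow DXA: "Patients are stratified based on their BMD DXA T-score into osteoporotic, fractured and non-fractured". Patients with a fragility fracture join the osteoporotic fractured group whatever their T-score. The comparison group is defined only by what it is not: "non-osteopenic and non-osteoporotic patients (hereafter referred to as healthy patients"). The Allocation section repeats the T-score bands and sets 30 participants per group.

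The Eligibility criteria section presents its two lists as the criteria for recruitment. Obesity is ruled out by "Body Mass Index (BMI) between 18.5-29.9 Kg/m^2". The exclusion list opens with "Hematopoietic system diseases;Ø Bleeding disorders;Ø Infections (also positive for HIV-HBV-HCV);Ø Neoplastic pathologies", continues with pregnancy or breast-feeding and alcohol, and ends with "Smoking (>10 cigarettes per day currently or previously);Ø Diabetes". The sentence after the list explains the last two items: "Smoking and diabetes conditions were excluded to minimize major confounding effects on immune, metabolic, and inflammatory parameters", because these could interfere with reading PBMC behaviour apart from bone status.

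The Intervention section makes PBMC viability, number, size and spontaneous osteoclast formation the test measures. T-cell subsets (Th1, Th2, Th17, Treg) and serum cytokines, including TNF-α, IL-17 and IFN-γ, are measured alongside.

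**The concern.** Two gaps in the exclusion list bear on the two sides of an accuracy estimate.

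**Reference side.** The protocol itself says that osteomalacia affects the T-score, and then uses the T-score to decide who has the target condition. Nothing in Primary objective, Allocation or Recruitment asks why BMD is low. A patient with osteomalacia and a T-score in the osteoporotic or osteopenic band satisfies the criteria and is counted as having that condition.

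**Test side.** Smoking and diabetes are excluded because they disturb immune, metabolic and inflammatory measures. Active autoimmune or chronic inflammatory disease could disturb the same measures and is not excluded. If it shifts PBMC behaviour for reasons unrelated to bone, part of any difference between groups may reflect that disease.

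At stake is the primary aim, the sensitivity and specificity of the PBMC test. With 30 per group, one participant whose result changes moves a group proportion by 1/30 = 3.3 percentage points (1/60 = 1.7 points if the two osteoporotic groups are pooled).

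**Working it through.** **Step 1: texts side by side.**

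| Condition | Protocol's remark | Eligibility criteria |
|---|---|---|
| Obesity | Affects T-scores (Introduction) | Ruled out by the BMI limit |
| Osteomalacia | Affects T-scores (Introduction) | Not listed |
| Other non-osteoporotic metabolic bone disease | Not named; the Introduction's list is open-ended | Not listed |
| Smoking above the limit, diabetes | Disturb immune, metabolic and inflammatory measures (Exclusion criteria) | Excluded |
| Infection, neoplasia, haematopoietic disease | No reason given | Excluded |
| Autoimmune or chronic inflammatory disease | Not named | Not listed |

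The Statistical methods section stratifies by T-score and gender and names no adjustment for these diseases. An analysis plan could add one, so that silence is not the finding. The finding rests on the eligibility list, which is protocol content.

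**Step 2: the plan's own figures.** The plan gives no prevalence of these diseases and no expected sensitivity or specificity, so there is no figure to reproduce on this point. The sample size of 120 comes from a chi-square calculation (w = 0.33, power 0.80, alpha 0.05). Neither the gap nor the fix changes an input to it.

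**Step 3: illustration.** All values here are assumptions. Let true sensitivity Se and specificity Sp both be 0.80. Let a share c of each group have an unexcluded disease, and let those patients test positive with probability q whatever their bone status. Then:

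- apparent sensitivity = (1 − c) × Se + c × q
- apparent specificity = (1 − c) × Sp + c × (1 − q)

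Example, c = 0.10 and q = 0.20: sensitivity = 0.90 × 0.80 + 0.10 × 0.20 = 0.74; specificity = 0.90 × 0.80 + 0.10 × 0.80 = 0.80.

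Results as sensitivity / specificity:

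| c | q = 0.20 | q = 0.50 | q = 0.80 | q = 1.00 |
|---|---|---|---|---|
| 0.05 | 0.77 / 0.80 | 0.785 / 0.785 | 0.80 / 0.77 | 0.81 / 0.76 |
| 0.10 | 0.74 / 0.80 | 0.77 / 0.77 | 0.80 / 0.74 | 0.82 / 0.72 |
| 0.20 | 0.68 / 0.80 | 0.74 / 0.74 | 0.80 / 0.68 | 0.84 / 0.64 |

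A share of 0.10 is 3 of 30 participants, and 0.20 is 6 of 30.

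**Step 4: reading it.** The direction depends on q, which the documents do not give. If affected patients behave like true negatives (q = 0.20), sensitivity is understated. If they nearly all test positive, sensitivity is overstated and specificity falls. If the disease sits only in the osteoporotic groups, the sensitivity figures apply and specificity stays at 0.80. The documents do not say how these diseases are spread across the groups.

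**The case against.** The strongest reply is that this is a design preference. The osteomalacia remark is background on the weakness of DXA and commits the protocol to no eligibility rule. The rationale sentence covers smoking and diabetes only. Infection, neoplasia and haematopoietic disease are excluded, so some control of inflammatory confounding exists.

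Much of this stands for the inflammatory part. A reader might infer that the protocol promises to protect all immune read-outs and breaks the promise; it makes no such general promise. A patient with inflammatory disease and a T-score below −2.5 is osteoporotic by the study's own standard, so a positive result there is a true positive by that standard. Expected outcomes also treats T-lymphocytes and pro-inflammatory cytokines as part of how osteoporosis arises. Excluding all such patients would narrow the range of patients studied for a test meant for screening.

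A reader might also infer that the Strengths and limitations section is false where it says "Although several confounding factors (e.g., BMI, comorbidities, substance use) are excluded by design". It is not: it claims that several confounders are excluded, and several are.

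Nor do the documents support a stated inflation of sensitivity. Every figure in the illustration is assumed. The Introduction relates PBMC viability to altered bone metabolism as well as osteoporosis, so patients with osteomalacia might test positive and leave apparent sensitivity unchanged. A shift of 0.06 (at c = 0.10, q = 0.20) is also below one standard error at n = 30: √(0.80 × 0.20 / 30) = 0.073. But bias is not sampling error, and more participants would not remove it.

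The reply does not remove the osteomalacia gap. The protocol names the condition as affecting the measure that defines its reference class, and the recruitment criteria let it through.

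**Conclusion.** The point holds in two parts of unequal strength.

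1. Osteomalacia and other non-osteoporotic metabolic bone disease should be handled. The protocol recognises the effect on T-scores, assigns classes by T-score or fragility fracture, and does not exclude these patients. They can be labelled osteoporotic or osteopenic and bias sensitivity and specificity.
2. Active autoimmune or chronic inflammatory disease is a possible, uncontrolled confounder of an immune-cell test. It is not an internal contradiction.

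The size and direction of the bias cannot be computed from the documents. Under the assumptions shown, with 5% to 20% of each group affected, apparent sensitivity ranges from 0.68 to 0.84 and apparent specificity from 0.64 to 0.80, against a true 0.80 for each. The actual shift could be negligible if these diagnoses are rare among those enrolled; a chart check would show that.

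A reader might conclude that enrolled participants with these diagnoses should leave the primary analysis. The documents do not support that. These participants met the criteria, enrolment began on 30 August 2024, and removing them now would be a post-enrolment exclusion.

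**What to change.** - **Remaining recruitment:** add to Exclusion criteria known osteomalacia or other non-osteoporotic metabolic bone disease, applied from the medical history.
- **All participants, including those already enrolled:** abstract from the chart any diagnosis of metabolic bone disease and any active autoimmune or chronic inflammatory disease. Do this without sight of the PBMC results.
- **Analysis:** keep the full eligible set as the primary accuracy analysis. Before the blind is broken, pre-specify a sensitivity analysis that excludes, or adjusts for, participants with these diagnoses, and report their number per group.

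The cost is one amendment, a chart check and one extra analysis. No new test is needed and the sample-size inputs do not change. A few candidates become ineligible, and the sensitivity analysis will be less precise because it uses fewer participants.
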